### Treatment fidelity

Following trial commencement, the trial physiotherapists can discuss any issues that arise with delivering the intervention with the research team. Trial physiotherapists can contact the research team through the trial by email or telephone. Additionally, regular meetings via Zoom are held with the trial research team and each intervention group of physiotherapists (separately). These regular meetings also allow the opportunity for therapists to provide feedback or discuss any issues arising. A random sample of treatment sessions (minimum of one for each therapist) will be audio recorded to allow an audit of intervention fidelity for each group. Each physiotherapist and physiotherapy clinic will provide only one of the two study interventions. Therapists’ case notes for each session, recorded via standardised templates, will also be used to evaluate intervention fidelity (e.g., the exercises and walking prescribed).

### Dealing with adverse events

Given the provision of walking and strengthening exercises, we expect transient increases in lower limb pain or swelling (including, but not limited to, the trial knee) due to increased structured physical activity. Trial therapists and participants are advised to report any adverse events to the study coordinator as soon as possible via documentation in treatment notes uploaded online in REDCap (therapists) as well as via email or telephone call to the study coordinator (therapists and participants). If needed, trial participation is continued in a revised manner (including the potential for additional treatment sessions for the problem), or treatment is discontinued and further medical intervention is arranged. Adverse events are formally collected via participant self-report following weekly intervention completion (12 weeks) and at the 6 and 12 month follow-up questionnaires.

### Outcomes

Table 5 provides the full list of outcome measures and time points of assessment. Our primary and secondary outcome measures are measured at baseline, 12 weeks, 6 and 12 months.

**Table 5 Tab5:** Summary of measures to be taken

Domain	Data collection instrument	Time points				
		Baseline	After 1st treatment session	12 weeks	6 M	12 M
**Descriptive data**						
Age, gender, weight, height, body mass index		X				
Duration of knee OA symptoms		X				
Educational level, postcode		X				
Treatment and medication use in past month		X		X	X	X
Problems in other joints		X				
Co-morbidities	Functional Co-morbidity Index	X				
**Primary outcome measures**						
Physical activity level	Average daily step count via wrist-worn accelerometry	X		X	X	X
OA knee symptoms in past 48 h	WOMAC Total score (includes pain, physical function, stiffness subscales)	X		X	X	X
**Secondary outcome measures**						
Average knee pain past week	11-point NRS	X		X	X	X
Average knee pain during walking past week	11-point NRS	X		X	X	X
Physical activity level	Daily minutes of sedentary, light, moderate, vigorous activity via wrist-worn accelerometry	X		X	X	X
Knee pain past 48 h	WOMAC pain subscale	X		X	X	X
Knee function past 48 h	WOMAC function subscale	X		X	X	X
Depression past week	4-item PROMIS depression subscale	X		X	X	X
Anxiety past week	4-item PROMIS anxiety subscale	X		X	X	X
Stress past month	4-item PSS	X		X	X	X
Fear of movement	Brief FOM questionnaire	X		X	X	X
Pain catastrophising	PCS	X		X	X	X
Health related quality of life	EQ-5D-5L	X		X	X	X
Knee perception	FREKAQ	X		X	X	X
Global rating of change	7 point ordinal scale			X	X	X
**Mediators**						
OA/activity Conceptualisation	Osteoarthritis and Physical Activity Conceptualisation Scale	X		X	X	X
Pain self-efficacy	PSEQ	X		X	X	X
Exploratory: Implicit movement bias	Implicit association task	X		X		
Exploratory: Implicit environmental bias	Distance estimation task Hill steepness estimation task	X		X		
Exploratory: Pain sensitivity to activity	Pain pre−/post- 6 min walk task	X		X		
**Exploratory objective factors and questionnaires (potential modulators/moderators)**						
Implicit motor imagery	Left/right judgement task	X		X		
Tactile acuity at the knee	Two point discrimination task	X		X		
OA pain conceptualisation	OA pain drawing task	X				X
Self-regulated learning ability	Items from the Motivated Strategies for Learning and Regulation of Learning questionnaires	X		X	X	X
**Resource use**						
Health care use^a^	Resource use associated with the delivery of the intervention. Self-reported use of health services and co-interventions; MBS; and hospital admissions and emergency department presentations from administrative datasets	X		X	X	X
Medication use^a^	Self-reported medication use and PBS data from administrative datasets	X		X	X	X
**Additional outcomes**						
Expectation of treatment outcome	5 point ordinal scale		X			
Treatment credibility	Modified Treatment Credibility/Expectancy Questionnaire		X			
Intention to exercise	7 point ordinal scales (commitment, motivation, determination to exercise)		X	X	X	X
COVID-19 impact on physical activity	7-point ordinal scale	X		X	X	X
Adherence	Self-rated adherence to walking and strengthening program, 11-point NRS and number of days in past week exercise performed			X	X	X
	Number of in-person sessions attended			X	X	X
	Number of telehealth sessions attended			X		
	Review of patient diary					X
Harms	Adverse events			X	X	X
Blinding	Participant blinding assessed via allocation guesses (and reasons); then forced choice					X
	Outcome assessor blinding (same method)			X		
	Therapist blinding (same method)					X^b^
Therapist related factors	Beliefs about exercise; self-rated via Therapist Beliefs about Exercise Questionnaire	X				X^c^
	Beliefs about pain; self-rated via Pain Attitudes and Beliefs Scale for Physiotherapists	X				X^c^
	Pain knowledge; assessed via rNPQ	X				X^c^
	Perceived intervention credibility; assessed via modified intervention credibility and expectancy questionnaire	X		X^d^		X^d^
	Perceived connection with participant; self-rated via 101-point NRS Connectedness Scale			X		

^a^Data on MBS, PBS and emergency department presentations and hospital admissions will be sourced from government-held administrative datasets for the entire 12 month follow-up period at its conclusion. ^b^Measured at end of trial (recruitment complete); aim is to determine if the ‘Best practice control group’ therapists thought they were the intervention group of interest. ^c^Measured at baseline (pre-training), post-training, and end of trial (recruitment complete). ^d^Measured after pre-trial training (baseline), after the first 12 weeks of treatment (pilot participant), mid-way through the trial (i.e., half-way through recruitment), and at the end of the trial (recruitment complete)

### Primary outcomes

The primary outcomes are: i) average daily step count assessed over 7 consecutive days via wrist-worn accelerometry (Actigraph GT9X Link, Pensacola, FL); and ii) overall knee symptoms measured via the Western Ontario and McMaster Universities (WOMAC) Osteoarthritis Index [62]. The primary timepoint for both outcomes is 12 months.

For daily step count, participants wear the accelerometer on their non-dominant wrist at all times (removal only for shower or during water-based activities). Data are collected from the device in 60 s epochs. A paper-based activity log is provided to participants to capture times they go to bed at night and get up from bed in the morning, as well as times the accelerometer was removed and then placed back on (particularly if taken off when sleeping). Valid wear time is operationalised as having ≥10 h of waking wear time for a minimum of 4 days (3 weekdays and 1 weekend day) [63, 64]. Average daily step count is calculated as the weighted average (5:2) of weekday and weekend step counts. We chose daily step count as a primary outcome based on its: i) health benefits in knee OA (increased physical activity via walking improves both pain and function [65], and even a moderate increase in physical activity [1000 steps/day] reduces risk of functional decline [66]); and ii) established reliability/validity in knee OA [67].

The WOMAC is a disease-specific self-report questionnaire that includes pain (5 items), stiffness (2 items), and physical function (17 items) subscales. Items are scored from 0 to 4, giving a range of possible scores from 0 (no symptoms or dysfunction) to 96 (maximal symptoms and dysfunction). It has demonstrated validity, reliability, and responsiveness [68]. The use of the total score for primary outcomes is supported by the scale creators.

### Secondary outcomes

The secondary outcome measures are:
i)Average knee pain over the past week rated using an 11-point Numerical Rating Scale, anchored with “0, no pain at all” to “10, worst pain possible” [47];ii)Average knee pain while walking over the past week using an 11-point Numerical Rating Scale, anchored with “0, no pain at all” to “10, worst pain possible” [47];iii)Knee pain over the past 48 h, via the WOMAC 5-item pain subscale score, with items scored from 0 to 4, giving a range of possible scores from 0 (no pain) to 20 (maximal pain) [62];iv)Knee function over the past 48 h via the WOMAC 17-item function subscale scores, with items scored from 0 to 4, giving a range of possible scores from 0 (no dysfunction) to 68 (maximal dysfunction) [62];v)Depression, assessed using the 4-item PROMIS depression subscale, with items scored on a 5-point Likert scale from “Never” (1) to “Always” (5), giving a range of scores from 4 to 20 (rescored using a T-score metric with a score of 50 representing the mean and 10 the standard deviation of a reference population), with higher scores reflecting greater depression [69];vi)Anxiety, assessed using the 4-item PROMIS anxiety subscale, with items scored on a 5-point Likert scale from “Never” (1) to “Always” (5), giving a range of scores from 4 to 20 (rescored using a T-score metric with a score of 50 representing the mean and 10 the standard deviation of a reference population), with higher scores reflecting greater anxiety [69];vii)Stress over the past month, assessed using the 4-item Perceived Stress Scale, scored on a 5-point Likert scale from “Never” (0) to “Very often” (4), giving a range of possible scores of 0 (no perceived stress) to 16 (maximal perceived stress) [70, 71];viii)Fear of movement, assessed using the 6-item Brief Fear of Movement for OA scale, scored on a 4-point Likert Scale from “Strongly disagree” (0) to “Strongly agree” [3], giving a range of possible scores of 0 (no fear of movement) to 18 (maximal fear of movement) [19];ix)Pain catastrophising, using the brief 4-item Pain Catastrophising Scale (PCS), scored on a 5-point Likert scale from “Not at all” (0) to “All the time” (4), giving a range of possible scores of 0 (no pain catastrophising) to 16 (maximal pain catastrophising) [72];x)Health related quality of life (HrQOL) using the EQ-5D five level instrument (EQ-5D-5L scale) [73]. The EQ-5D-5L measures HrQOL across five dimensions (mobility, self-care, usual activities, pain/discomfort and anxiety/depression) each with five possible response options ranging from no problems (1) to unable or extreme problems (5). It also includes a 100-point global health rating using a visual analogue scale (EQ-VAS) ranging from 0 (worst imaginable health) to 100 (best imaginable health).xi)Knee perception using the Fremantle Knee Awareness Questionnaire (FREKAQ), involving 9-items, scored on a 5-point Likert scale from “Never” (0) to “Always” (4) with giving a range of possible scores of 0 (no perceptual dysfunction) to 36 (maximal perceptual dysfunction) [74];xii)Global rating of change, scored on a 7-point Likert scale for “Overall change in your study knee since you began the study”, “Overall change in physical activity”, “Overall change in pain”, and “Overall change in physical function” from “Much worse” to “Much better”. Responses will be dichotomised to “Improved” (“Moderately better” and “Much Better”) and “Not improved” (all other choices) [75];xiii)Average daily minutes of sedentary, light, moderate, and vigorous activity and volume (intensity x time) from the wrist-worn accelerometry using two published methods for cut-point-based analysis: Troiano cut-points [63, 76], and those from Smuck et al. (2017) [77].

### Demographic and descriptive data

At baseline, the following data are collected: i) age; ii) sex; iii) height and weight; iv) postal code; v) educational level; vi) duration of symptoms, vii) presence of co-morbidities (via the Functional Co-morbidity Index [78]), viii) pain in others parts of the body, ix) medication use over the past month; and x) interventions received during the past month.

### Mediators

#### Primary mediators

i)Conceptualisation of OA and physical activity, assessed using the Knee OA and Activity Conceptualisation Scale (OACS), which includes 33 items scored on a 5-point Likert scale from “Strongly agree” (1) to “Strongly disagree” (5), with scores ranging from 33 (low conceptualisation) to 165 (high conceptualisation);ii)Pain self-efficacy assessed using the Pain Self-efficacy Questionnaire (PSEQ) [79], which includes 10 items scored on a 7-point Likert scale from “Not at all confident” (0) to “Completely confident” (6), with scores ranging from 0 (no confidence to perform activity despite pain) to 60 (maximal confidence to perform activity despite pain).

### Exploratory mediators (if sufficient data are available)

i)Implicit movement bias: An implicit association test based upon established methodology [80] will be used to evaluate the presence of positive or negative movement bias. Using 2 target categories (image of knee movement – ‘active’ vs image of knee resting – ‘rest’) and 2 attribute categories (‘safe’ and ‘danger’), participants sort images into categories: responses are faster/with fewer errors if the target and the attribute category are associated for that person, and are slower/with more errors if they are not [80], allowing determination of negative movement bias (faster movement–‘danger’ and rest–‘safe’ pairings) and positive movement bias (faster movement–‘safe’ and rest–‘danger’ pairings).ii)Implicit environmental bias: Perceptual shifts in relation to the environment will be assessed via estimation of the distance to a target for a walking task [81] and via estimation of hill steepness [82], the latter using virtual reality (equivalent responses to real-life) [45]. Errors between estimated and actual distance/steepness are used.iii)Pain sensitivity to activity, assessed via calculating the change in knee pain intensity ratings (11-point NRS) from pre- to post-standardised 6 min walk test [83].

### Additional measures

#### Exploratory objective factors and questionnaires (potential modulators/moderators)

These include: i) implicit motor imagery performance, assessed via left/right judgement tasks (accuracy and response time) for images of feet and of hands (control) [84] using the Recognise App (NOIgroup Pty Ltd) on an iPad; ii) tactile acuity at the knee assessed using callipers to determine the two-point discrimination threshold at the medial knee [85]; iii) abstract OA pain conceptualisation as assessed using an OA pain drawing task whereby participants are asked to draw their understanding of OA and why it hurts; iv) Self-regulated learning ability, assessed using 7 items from the Motivated Strategies for Learning Questionnaire [86], with items rated on a 7-point Likert scale from “Not true at all for me” to “Very true for me”.

#### Treatment expectations/credibility

Expectation of treatment outcomes are assessed using a 5-point ordinal scale in response to the question “What effect do you think this treatment will have on your knee problem”, with choices from “no effect at all” to “complete recovery”. A modified Credibility/Expectancy Questionnaire (CEQ) [87] is also used to assess treatment credibility via 4 questions: “How logical does this treatment offered to you seem”; “How successful do you think this treatment will be in reducing your knee OA symptoms”; “How successful do you think this treatment will be in increasing how much you move”; “How confident would you be in recommending this treatment to a friend who experiences similar problems”. These are rated on a 9-point Likert scale from “not at all logical/useful/confident” to “very logical/useful/confident”.

#### Intention to exercise

Intention to exercise is assessed via 3 questions: “I am committed to engage in physical activity over the next 2 weeks”; “I am motivated to engage in physical activity over the next 2 weeks” and “I am determined to engage in physical activity over the next 2 weeks” [88]. A 7-point Likert scale from “very strongly disagree” to “very strongly agree” is used.

#### Measurement and valuation of resource use

Total costs associated with delivering the intervention, including resources used in a) the development and provision of face-to-face, evidence-based education sessions and b) the development and provision of home activities and weekly development goals, workbook and telephone contacts, will be measured and valued using appropriate unit costs. Health service utilisation data for the participants, including in-patient hospital stays and emergency department presentations will be accessed from relevant state-based health department administrative records. Individual-level Medicare Benefits Schedule (MBS) and Pharmaceutical Benefits Scheme (PBS) data (including specialist consultations, visits to general practitioners, and access to prescription pharmaceuticals) will be collected from administrative databases held by Services Australia following informed consent from trial participants. Any additional services accessed outside of these programs will be collected via participant self-report. Following relevant guidelines, costs for relevant healthcare resources will be sourced from publicly available published data (including the National Health Cost Data Collection, MBS and the PBS) [89–92].

#### Adverse events

Participants are asked to provide details on the nature of the event, how long it lasted, and what action they took. For the purpose of this trial we define adverse events as “any untoward medical occurrence in a patient or clinical investigation participant administered a treatment and which does not necessarily have a causal relationship with this treatment. An adverse event can therefore be any unfavourable and unintended sign (including an abnormal laboratory finding), symptom, or disease temporally associated with the use of a treatment, whether or not related to the treatment”. The trial physiotherapists (or study coordinators, if contacted by participants directly) record details of the adverse event, including whether it was related or unrelated to the study intervention.

#### Adherence

Adherence is assessed in each group via a review of attendance records for in-person physiotherapy appointments and telephone/videoconferencing physiotherapy sessions. Adherence to the prescribed walking programs is self-reported by the participant via 11-point Likert scale (0 means “strongly disagree” and 10 means “strongly agree”) in response to three statements: “I have been doing the number of walks each week as recommended”; “Within each walk, I have been walking the distance/time/steps as recommended”; and, “Within each walk, I have been walking at the recommended intensity”. Participants are also asked to indicate on how many days in the past week they walked for exercise (options of 0 to 7 days). Adherence to the strengthening program is also self-reported using similar assessment (“I have been doing the strengthening exercises each week as recommended”; “For each exercise, I have been doing the sets/repetitions as recommended”; and, “In the past week, on how many days did you perform the strengthening exercises?”). When available, adherence will also be informed via review of participant workbook, walking program, and strengthening program diaries that they keep over the 12 months.

#### COVID-19 impact on physical activity

Self-reported impact of COVID-19 on physical activity is assessed via the question, “During the past 4 weeks, has COVID-19 influenced your usual physical activity levels/exercise routines?” with dichotomous response options of “Yes” or “No”. If participants answer yes, they self-report the extent to which COVID-19 has influenced usual physical activity levels/exercise routines on a 6-point Likert scale ranging from “Large reduction” to “Large increase”. Additionally, trial coordinators in Adelaide and Melbourne keep weekly records of the state recommendations and/or restrictions in relation to travel, physical activity, use of public transport, ability to leave the home, etc.

#### Blinding

Following an explanation to participants that clinical trials typically have an intervention of interest (active intervention) that is tested to see if it is better than the other intervention (control intervention), they are asked to identify which treatment they believe they received (choices: “Active intervention”, “Control intervention”; or “Don’t know”). If they answer, “Don’t know”, they are then asked to make a forced choice decision between active and control intervention [93]. Free text responses are collected regarding the reasons behind their choice (“What led you to believe that you received this treatment?”) and if they were unblinded (“If you discovered which treatment [active or control] you received, please tell us when and/or how you found out.”). Treating physiotherapists are also asked at trial cessation whether they thought they were in the active or control intervention group using similar methodology (three options including “Don’t know”, followed by forced choice and free text responses).

#### Therapist related factors

Therapist’s beliefs about exercise and about pain will be assessed via the modified Therapist Beliefs about Exercise Questionnaire [94] and the modified Pain Attitudes and Beliefs Scale for Physiotherapists (PABS-PT) [95], respectively. Therapist’s pain knowledge will be assessed using the revised Neurophysiology of Pain Questionnaire (rNPQ) [96] in the EPIPHA-KNEE group only to preserve therapist blinding in the Control group. Therapist’s perceptions of intervention credibility will be assessed using the Modified Intervention Credibility and Expectancy Questionnaire [87]. Last, therapist’s perceived connection with the participant will be self-rated using a 100 mm VAS Connectedness Scale (0 = no connection at all; 100 = maximum connection).

### Trial sample size

The Osteoarthritis Research Society International (OARSI) recommends an effect size (d = mean difference/SD_difference_) of 0.5 as the minimal clinically important difference (MCID) for outcomes in OA trials [97]. Past work has estimated that PSE increases physical activity by 1165 steps/day (SD = 985) in people with back pain, producing a large effect (d = 1.18) [39]. Given ~ 850 steps/day increase in knee OA populations after intervention (SD_difference_ = 950) [98] and our pilot data, we anticipate a moderate-large effect in the PSE group and a small effect in the control group at 12 months; consistent with a between group effect size of 0.5. Analysing these data using linear mixed effects modelling, to detect an effect size of d = 0.5 for physical activity using alpha = 0.05, power = 0.90, 4 time points, repeated measures correlation = 0.7, and 20% loss to follow-up [98], 156 participants (78/group) are needed. To additionally adjust for clustering based on therapist (~ 12 therapists/group; ~ 6.5 patients each; ICC = 0.05 [99]), 198 participants (99/group) are then required. The MCID for WOMAC Total at 12 months in people with knee OA undergoing an exercise intervention is 11.5 [100, 101], and given a between group SD from our pilot data of 13.8 (d = 0.83) [42], we are also sufficiently powered for this outcome. We did not adjust the alpha level for multiple comparisons (two primary outcome measures) in our power analysis, but we will present unadjusted *p*-values and confidence intervals for meaningful interpretation.

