#### Primary analysis

Data will be analysed using intention-to-treat principles with the trial biostatistician blinded to group allocation. We will use linear mixed effects models with random intercepts for individuals (to account for correlation for repeated measures) and will analyse the effect of treatment separately for each outcome. The model will include terms for stratification factors of sex and site. A time-varying, group specific effect (for each group) will be included as covariates for participants with restricted physical activity as a result of location-specific COVID-19 restrictions (based upon official activity restrictions and/or participant reported restrictions; assessment detailed above). Statistical significance will determine whether group-specific covariates or even any COVID-19 related effects are warranted for model parsimony. Multiple imputation will be used for missing data if the assumptions are reasonable [102]. We will construct linear contrasts to compare the adjusted mean change in outcome from baseline to each time point between the EPIPHA-KNEE group and the control group (and 95% confidence interval) to obtain estimates of the intervention effect. We will analyse primary and secondary outcomes without adjustment for multiple measures, but we will present unadjusted *p*-values and confidence intervals for all pre-specified analyses [103, 104] so readers can make adjustments (e.g., Bonferroni) at the level of Type I error control that they wish, at risk of making Type II errors.

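### On the printed definition of d, 198 participants give about 80% power for the 12-month change in steps, not 90%; the stated N matches a calculation that discounts for the 0.7 correlation a second time

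*Protocol article*

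**What the plan says.** All the sample-size inputs are in the protocol's Trial sample size section.

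- The clinically important difference is given as "an effect size (d = mean difference/SD_difference_) of 0.5".
- The steps inputs are changes over time. A back-pain study is cited for an increase of 1165 steps/day with SD 985, reported as d = 1.18 (1165/985 = 1.18). For knee OA the text reads "Given ~ 850 steps/day increase in knee OA populations after intervention (SD_difference_ = 950".
- The between-group target is reasoned from effects of this kind: "we anticipate a moderate-large effect in the PSE group and a small effect in the control group at 12 months", described as "consistent with a between group effect size of 0.5".
- The calculation uses alpha 0.05 and "power = 0.90, 4 time points, repeated measures correlation = 0.7, and 20% loss to follow-up", giving 156 participants (78 per group). Therapist clustering (about 6.5 patients per therapist, ICC 0.05) raises this to 198 (99 per group).

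Two other sections fix what the power should refer to. Under Primary outcomes: "The primary timepoint for both outcomes is 12 months". Under Primary analysis, the contrasts "compare the adjusted mean change in outcome from baseline to each time point" between the two groups.

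**The concern.** The paragraph combines two ingredients that do not belong together. An SD of change already reflects the within-person correlation, because Var(change) = 2(1 − ρ)σ², where σ is the SD at a single visit. Once d is standardised on that SD, the correlation and the number of visits earn no further reduction in the sample size for a simple difference in change. Yet the four time points and the correlation of 0.7 are listed as inputs, and the resulting N is smaller than d = 0.5 alone would require.

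At stake is the accuracy of a stated design property for a co-primary outcome. A reader who takes 90% at face value would put the chance of missing a difference of 475 steps/day at 10%. On the printed definition it is nearer 20%.

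**Working it through.** **Inputs.** d = 0.5 on the SD of change; SD of change 950 steps/day; alpha 0.05 (sidedness is not stated, two-sided assumed); power 0.90; 4 time points; ρ = 0.7; 20% loss; 6.5 patients per therapist; ICC 0.05; 1:1 allocation; 99 per group.

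**1. Reproducing the plan's figures.**
- Two-sample normal formula: 2 × (1.96 + 1.2816)² / 0.5² = 84.06 per group.
- Variance factor for the mean of four equally correlated visits: (1 + 3 × 0.7)/4 = 0.775. Then 84.06 × 0.775 = 65.15.
- Loss as a multiplier: 65.15 × 1.2 = 78.2 (stated: 78).
- Design effect: 1 + (6.5 − 1) × 0.05 = 1.275. Then 78 × 1.275 = 99.45 (stated: 99).

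Both stated figures are matched with rounding down. Other routes tried do not give 156 in total:

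| Route | Total before clustering |
|---|---|
| No discount | 204 (×1.2) or 214 (/0.8) |
| Factor 0.775 with loss as /0.8 | 166 |
| Change factor 2(1 − ρ) = 0.6, with /0.8 | 128 |
| 1 − ρ² = 0.51, with /0.8 | 108 |
| Mean of three follow-ups, factor 0.8 | about 161–163 (×1.2) or 170 (/0.8) |

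**2. Why the factor does not fit.** The value 0.775 is the variance of a four-visit mean relative to the variance at one visit. It therefore needs d on a single-visit SD and a between-group difference averaged over all visits. The four scheduled assessments include the pre-randomisation baseline, which cannot carry a treatment effect. The planned contrast is instead the change from baseline to 12 months.

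**3. Power at 198 with d as printed.**
- Effective number per group: 99 × 0.8 / 1.275 = 62.1.
- Power: Φ(0.5 × √(62.1/2) − 1.96) = Φ(0.827) = 79.6%.
- Crediting the earlier visits of those lost (generalised least squares, equal correlation 0.7): 80.8% if all losses come straight after baseline, 81.8% if spread evenly, 82.4% if only the 12-month visit is lost.
- Baseline constrained or adjusted, with variance factor (1 + 0.7)/2 = 0.85 relative to the SD of change: Φ(0.5/√0.85 × √(62.1/2) − 1.96) = 85.6%.

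**4. Difference detectable with 90% power.** 3.2415 × √(2/62.1) = 0.582 SD of change; 0.582 × 950 ≈ 553 steps/day. For comparison, 90% power at 0.5 would need 84.06 / 0.8 × 1.275 = 134 per group.

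**5. The alternative reading, d on the single-visit SD.** The SD of change is then √0.6 times that SD, so power for the 12-month change is Φ(0.5/√0.6 × √(62.1/2) − 1.96) = 94.9%. The target in steps is 0.5 × 950/√0.6 ≈ 613 steps/day.

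**6. Loss to follow-up.** Multiplying by 1.2 does not replace a 20% loss; dividing by 0.8 does. On the plan's own route this gives 65.15/0.8 = 81.4 per group rather than 78. With 62.1 effective per group, power is 88.6% even for the four-visit average.

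**The case against.** The strongest reply is that the shortfall depends on which SD was meant. The paragraph labels its SDs in three ways: a plain SD for the back-pain study, an SD of the difference for knee OA, and a between-group SD for the WOMAC. Listing ρ = 0.7 and four time points suggests that the planner may have had d on the ordinary outcome SD in mind. The figure of 475 steps/day is not printed, and 0.5 is only called compatible with the anticipated effects. This stands in part. A reader might infer that 90% power is unattainable whatever was meant, and the document does not support that: on the single-visit SD, power exceeds 90%. But that reading contradicts the definition of d that the paragraph prints and raises the target to about 613 steps/day, so the paragraph still needs correcting.

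The formula is also an inference. Rounding up at each step of the same route would give somewhat larger numbers. The two-stage match is strong evidence but not proof. The power in step 3 does not depend on it, since it uses only the printed d, N, loss and clustering inputs.

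Three further readings are tempting and do not hold.

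- A reader might extend the criticism to the WOMAC. The section claims adequate power only for its outcome-specific difference of 11.5 points with SD 13.8. There d = 0.83, and 62.1 effective per group gives about 99.6% power. The claim is sound.
- A reader might argue for still lower power from therapist-level degrees of freedom. The Primary analysis section describes random intercepts for individuals only, so no such figure is attached to the stated model.
- A reader might conclude that a null result will be misread. The protocol commits to reporting confidence intervals, and these, not design power, show which differences a null result excludes.

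**Conclusion.** The stated 90% is wrong as written, conditional on the printed definition of d. For the 12-month change in steps at 0.5 SD of change (475 steps/day), power is about 80%, or 81–82% when partial follow-up is credited. A baseline-constrained or baseline-adjusted model would bring it to about 86%, still short of 90%. The type II error is thus roughly twice the stated 10% for the simple change contrast, and about 14% with baseline constrained or adjusted.

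These figures assume a two-sided test, the same SD of change in both groups, equal correlation of 0.7 between visits, and the plan's own 20% loss and design effect of 1.275. If the single-visit SD was intended, the power is understated and the error lies in the definition of d. Either way, the effect size, the power and the primary contrast in the text do not agree with one another.

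**What to change.** Keep 198 participants and reword the sample-size paragraph, carrying the same wording into the analysis plan:

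- State which SD standardises d = 0.5, and that the power refers to the between-group difference in change from baseline to 12 months.
- If it is the SD of change, state either about 80% power for 0.5 SD (475 steps/day) or 90% power for about 0.58 SD (about 553 steps/day). If the analysis will constrain or adjust for baseline, about 86% for 0.5 SD may be given instead, with that model named.
- If it is the single-visit SD, correct the definition of d and give the target as about 613 steps/day, with about 95% power.
- Allow for loss as n/0.8.

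The WOMAC statement can stay. The cost is a text change, with no added participants or procedures. The downside is that, on the printed definition, the stated power becomes less favourable.
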